## **Follow-up of ADEs**

Study Investigators or other delegated team member shall follow-up on all ADEs (including those involving participants who have been discharged from the study) involving an AE and report in accordance with the above sections. Investigators will ensure that supplemental investigations are conducted in all follow-ups to help determine the nature and/or causality of ADEs. Investigators shall update, sign, and date the ADE reports as new and additional follow-up information become available.

## **Adverse Device Effect Reporting**

The sponsor assumes responsibility for appropriate reporting of ADEs to the regulatory authorities. The sponsor will also report suspected unanticipated SADEs to clinical site investigators. The investigator (or sponsor where required) must report unanticipated SADEs to the IRB that approved the protocol unless otherwise required and documented by the IRB.

All SADEs and SAEs occurring during the study must be reported to the appropriate sponsor contact person by study-site personnel within twenty-four (24) hours of their knowledge of the event.

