## 5.5 Product Support

A selection of patient services will be provided over the course of the study. Participants will be expected to complete two calls with a behavioral specialist: the Treatment Orientation Call will be completed prior to the start of intervention and a wrap-up call completed at the end of the intervention. The Treatment Orientation Call is intended to help introduce the participant to the nature of the treatment and assess readiness to engage in behavioral therapy. In this call, participants will also receive education on evidence-based behavioral strategies for NAFLD treatment that are not yet fully integrated into BT-NCBT-00x, such as the benefit of reducing dietary intake of saturated fat and replacing with monounsaturated and polyunsaturated fatty acids. The wrap-up session is intended to allow the Better Therapeutics team to gather feedback about participants' experiences using the intervention.

The study population will also be monitored by a Nurse Practitioner to assess participants' engagement and biometric progress. Users who are not meeting expected thresholds for engagement or biometric progress will be offered additional support in the form of a call with a behavioral specialist or nurse practitioner to help identify barriers to behavioral therapy and develop a plan for addressing these potential obstacles to improve treatment adherence and efficacy. Sample screen images of support messages and call scheduling ability in the App can be seen in Appendix 17.3.

A product support specialist will be available over the length of the study to provide support for participants who need help using BT-NCBT-00x. If a participant's needs are beyond the scope of technical product support, the product support specialist will refer the participant to the clinical care team for behavioral support. In addition, a behavioral support specialist may proactively reach out to patients to offer more support to help them get the most out of using BT-NCBT-00x. Participants will be free to accept or turn down any offer of support.

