| MRI-PDFF (to be done after Fibroscan)                          | X                       |                                                  | X                                                             |
| Review & confirmation of participant eligibility by PI         | X                                   |                                                  | X                                                             |
| Research staff refers eligible participants using Study Portal | X                                   |                                                  |                                                               |
| AE Reporting                                                   | X                       | X                                    | X                                                 |
| Installation of App & completion of first-time user experience |                                     | X                                    |                                                               |

|                                                                     |  |                                |  |
|---------------------------------------------------------------------|--|--------------------------------|--|
| Study staff contacts patient to schedule post-treatment visit & MRI |  | X                  |  |
| Healthy Days Measure ( HRQOL-04 )                            |  | X 
Day 1 and 76 |  |
| Net Promotor Score                                                  |  | X 
Day 85       |  |
| Treatment Experience Survey                                         |  | X 
Day 80       |  |

X - Patients may be identified during clinic visits, through pre-screening in patient database, or other IRB approved recruitment methods

X - MRI must be completed prior to patient being referred to begin treatment

X - Assess and document serious adverse events

X - Assess and document serious adverse events and adverse events

X - Participant's completion of onboarding and first time user experience marks treatment Day 1

X - This will begin on Day 74

X - Surveys are automatically dispensed to participants in-App on designated days

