## 6. Adverse Event Reporting

### 6.1 Definition of Adverse Events and Serious Adverse Events

AEs will be assessed throughout the study. SAEs will be assessed from the time of signing the informed consent form and AEs will be assessed starting at the time of starting the intervention.

An AE is any untoward medical occurrence in a participant or clinical study participant, temporally associated with the use of study intervention, whether or not considered related to the study intervention. An AE can therefore be any unfavorable and unintended sign (including an abnormal laboratory finding), symptom, or disease (new or exacerbated) temporally associated with the use of study intervention.

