## **14. Risks and Benefits**

The risks from participating in this study are minimal. The App, BT-NCBT-00x, asks questions about beliefs related to personal health that participants may find create some personal discomfort in answering. BT-NCBT-00x will provide recommendations for increased consumption of fruits, vegetables, whole grains, nuts, seeds, beans and legumes. The increased consumption of these types of foods could result in increased gastrointestinal gas and some physical discomfort.

BT-NCBT-00x also encourages gradual increases in physical activity of the participants' choosing. The engagement in physical activity comes with some risk for injury. However, the level of activity recommended by BT-NCBT-00x is consistent with standard of care guidelines and does not introduce risk beyond what is experienced in standard care.

If participant has comorbid conditions including type 2 diabetes or hypertension, and responds favorably to BT-NCBT-00x and make substantive changes while on medications for reducing blood glucose and/or blood pressure, the participant may experience transient and reversible drops in blood glucose and/or blood pressure that may require the participant to decrease medication usage under the guidance of a physician. Encouraging the participant to engage in self-monitoring of these biomarkers, if applicable, while using BT-0x is intended to mitigate these risks by enhancing the participant's awareness of blood glucose or blood pressure changes. Participants will be given the opportunity to self-monitor blood glucose and/or blood pressure if they indicate the presence of these conditions in treatment onboarding.

Engagement with BT-NCBT-00x may result in positive changes in behavioral habits related to diet, exercise and the management of stress. The results of changes in weight will be available to participants to view within BT-NCBT-00x and may provide participants insight into their health.

Delegated staff members at Arizona Liver Health will refer patients to the study and are registered study associates. If an AE is reported or discovered by a study associate, they will ensure participants receive appropriate care for any AEs experienced during the study period irrespective of their cause.

Given that the potential risks incurred in this study are minimal and there is a chance for increased knowledge and capacity for health promoting behaviors, the risk-to-benefit ratio is weighted towards greater benefits.

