## 17. APPENDICES

### Appendix 17.1: Study Enrollment Landing

[figure not shown][figure not shown]

Congratulations, you've completed all the requirements and are ready to begin the study!

[figure not shown][figure not shown]

This study is exploring a behavioral treatment for nonalcoholic fatty liver disease (NAFLD) and nonalcoholic steatohepatitis (NASH).

[Start Now](#)

What does a study participant need to do?

- Download the mobile app (Android or iOS)
- Complete weekly lessons designed to help you improve your liver health and examine ideas that may be holding you back
- Learn skills and practice new ways of eating and living
- Track your health numbers and get feedback
- Return to Arizona Liver Health clinic in 3 months to repeat blood work and imaging

Have questions?  
Contact the Study Coordinator at  
[contact]

[Create account](#)

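### Adverse events must be assessed throughout Days 1 to 90, but no site contact is scheduled before Day 74 and almost nothing routes events heard by sponsor staff to the investigator

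*Protocol*

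**What the plan says.** **Assessment period.** Section 6.1 states that "AEs will be assessed throughout the study", with SAEs collected from consent and AEs from the start of the intervention. The AE row of Table 1 (section 5.6) is ticked for D1 to D90 and for D90 to D104, and its footnote for both columns reads "Assess and document serious adverse events and adverse events".

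**Site contact.** The only site contact that Table 1 places in D1 to D90 is "Study staff contacts patient to schedule post-treatment visit & MRI", with the footnote "This will begin on Day 74". The enrollment page in Appendix 17.1 tells participants: "Return to Arizona Liver Health clinic in 3 months to repeat blood work and imaging".

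**Sponsor contact.** Under section 5.5 and the synopsis (Study Design), a sponsor nurse practitioner monitors engagement and biometric progress. Behavioral specialists hold support calls and the wrap-up call, and a product support specialist is available throughout. For needs beyond technical help, "the product support specialist will refer the participant to the clinical care team for behavioral support".

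**Reporting duties.** Sections 6.5 and 6.6 give grading of severity and causality to the investigator. Section 6.7 requires SAEs to reach the sponsor within 24 hours of notification, without saying whose. Section 6.9 says that SADEs and SAEs "must be reported to the appropriate sponsor contact person by study-site personnel within twenty-four (24) hours of their knowledge of the event". The same part of section 6.9 obliges the sponsor to tell site investigators of suspected unanticipated SADEs. Section 14 has a duty that begins "If an AE is reported or discovered by a study associate"; what it requires is that the participant receives appropriate care.

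**The concern.** The protocol fixes a continuous assessment period, then a contact schedule and reporting rules that may not deliver it. An AE in the middle of treatment would reach the investigator only if the participant reported it unprompted, recalled it at the end, or told a sponsor employee who chose to pass it on.

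Safety is part of the secondary objective, and section 11.3 counts as treatment-emergent any AE after App use begins. The risks named in section 14 (gas and abdominal discomfort, activity injuries, transient falls in glucose or blood pressure) include short-lived ones that are easily forgotten over three months. With about 20 participants, a few missed events would visibly change the table. A low count could mean low risk or little enquiry, and a reader could not tell which.

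This is not a matter for the SAP, which can only tabulate what was captured.

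**Working it through.** The protocol gives no figure of its own on this point. The check is a reading of passages side by side, with day arithmetic.

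**1. Days without scheduled site contact.** Treatment runs from Day 1 to Day 90, and the first scheduled site contact begins on Day 74 (Table 1). Days 1 to 73 are 73 days, and 73 / 90 = 0.81. That contact is for booking. The first scheduled visit with AE assessment is at D90 to D104, so recall may span up to about 104 days.

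**2. Could the App fill the gap?** The Treatment Experience Survey (Day 80), Healthy Days Measure (Days 1 and 76) and Net Promoter Score (Day 85 in section 5.6) contain no AE question. The Healthy Days items count days of poor health but do not ask what happened. By the key to Table 1, in-App activities need no research staff. Section 13 releases App server data to study personnel for outcome analysis, de-identified. As written, the App is not a route by which the site detects AEs.

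**3. Who can hear an event, and where must it go?**

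| Who hears it | Written route to the investigator |
|---|---|
| Investigator or site staff | Present (sections 6.7, 6.9) |
| Sponsor, if a suspected unanticipated SADE | Present (section 6.9) |
| Sponsor nurse practitioner, behavioral specialist or wrap-up caller, any other AE, SAE or ADE | None found |
| Sponsor product support specialist, any other AE, SAE or ADE | None found; the only referral is for behavioral support (section 5.5) |

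**4. The 24-hour trigger.** Section 6.7 and the synopsis (Safety Assessments) count from notification or notice and name no party. Section 6.9 counts from knowledge by study-site personnel. For an SAE first told to sponsor staff, the section 6.7 clock may be running while the section 6.9 clock is not.

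**5. Illustration only.** Event risks and capture rates here are assumed; neither is in the protocol. With 20 participants, true risk p and capture fraction c, the chance of recording at least one case is 1 − (1 − p·c)^20.

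| Assumed p | c = 1 | c = 0.9 | c = 0.7 | c = 0.5 |
|---|---|---|---|---|
| 5% | 0.64 | 0.60 | 0.51 | 0.40 |
| 10% | 0.88 | 0.85 | 0.77 | 0.64 |

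For example, at p = 5% and c = 0.5: 1 − 0.975^20 = 1 − 0.60 = 0.40. For a common event, if 40% of 20 participants (8) truly had one, capture of 50%, 70% or 90% would record 4.0, 5.6 or 7.2 on average.

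**The case against.** Four points on the other side carry weight.

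- **Sponsor duty.** A reader might infer that sponsor staff have no duty towards the investigator and that all reporting runs from site to sponsor. Section 6.9 contradicts this for suspected unanticipated SADEs, and it also foresees the sponsor reporting to the IRB where required. The gap concerns every other event, including the foreseeable, mostly non-serious ones in section 14.
- **The SAE clock.** A reader might infer that the clock never starts when sponsor staff hear first. The documents do not support that. The sponsor is itself the recipient of the 24-hour report, and section 6.7 does not limit notification to the site. What may be delayed is the investigator's assessment and IRB report.
- **Undercounting.** No scheduled contact is not no contact. Participants have a coordinator to call, continue usual care, are mostly recruited from the site's own clinics, and have AEs assessed at D90 to D104. Hospitalizations are less likely to be forgotten than minor discomfort. Under-recording is a risk, not something that the documents show.
- **Wording of roles.** Section 14 says that site staff are study associates, not that only they are. Section 6.9 (Documenting ADEs) allows a delegated team member to identify ADEs without limiting this to the site. The behavioral-support referral in section 5.5 is not an AE rule and does not divert AEs away from the investigator.

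These points narrow the finding. They do not supply a route: no passage delegates AE identification to the sponsor's support staff or tells them to forward what they hear. How often to ask about AEs in a small study described as minimal risk is partly a matter of choice, but a forwarding duty and one question in existing contacts do not depend on that choice.

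**Conclusion.** The concern holds in limited form. AE assessment is required throughout treatment, 81% of that period has no scheduled site contact, and, outside suspected unanticipated SADEs, no text carries events known to sponsor staff to the person who must grade them. Followed exactly as written, the protocol can leave such events out of the treatment-emergent AE summary. Sections 6.7 and 6.9 also disagree on what starts the 24-hour clock.

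The 73 days follow directly from Table 1. The effect on the AE count cannot be derived, because it depends on unknown event rates and on how much spontaneous reporting and end-of-study recall recover. A claim that events will be missed, or that the table will be biased by a stated amount, would go beyond the documents. The change is worth making because it is cheap and safety is a stated objective.

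**What to change.** 1. In sections 5.5 and 6, require sponsor support staff (product support, behavioral specialists, nurse practitioner, wrap-up caller) to forward any untoward event they hear of to the investigator: potential SAEs and SADEs on the protocol's existing 24-hour timeline, other AEs promptly.
2. Reconcile sections 6.7 and 6.9 on whose awareness starts the 24-hour clock, and cover the case in which sponsor staff are first to know.
3. Add one scripted, non-leading AE question to contacts that already exist (support calls, the scheduling contact from Day 74 and the wrap-up call), alongside the assessment already ticked at D90 to D104.

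The cost is protocol wording, a short script and brief training of sponsor support staff. No new visits or staff are needed. The downside is a somewhat higher recorded AE count, with some extra review for the investigator.

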## **7. Participant Compensation**

All participants will be compensated for participation based on completion of study milestones depending on study activities completed.

## **8. Study Terminations**

Participants are free to withdraw from the study at any time. The study principal investigator may exercise judgment to terminate a participant's involvement in the study if it is felt that continued participation might be harmful to the participant.

## **9. Sample Size**

The primary study population consists of approximately 20 male and female adult participants (18 – 75 years old), with a diagnosis of nonalcoholic fatty liver disease (NAFLD) or nonalcoholic steatohepatitis (NASH), and who satisfy the inclusion and exclusion criteria. Only those who meet PDFF  $\geq 10\%$  will be included in the primary endpoint analysis.

Sample size calculations are estimated for the primary analysis population, i.e. those who satisfy all inclusion/exclusion criteria and have a baseline PDFF  $\geq 10\%$ .

The sample size was calculated by referencing the mean absolute change in steatosis and standard deviation reported in a 2019 JAMA review of the impact to behavioral weight loss interventions on clinical markers of NAFLD (Koutoukidis et al., 2019). The average mean absolute change in steatosis was -2.4 and mean standard deviation was 1.6. Using these results, it was determined a sample size of approximately 8 participants would provide approximately 90% power, assuming an alpha of 0.05. To account for up to a 20% attrition rate, a minimum of 10 participants are required.

To ensure inclusion of a mix of patients with either NAFLD or NASH, a total of approximately 20 participants will be enrolled. It's expected that up to 50% of fully eligible participants will fail to meet the MRI-PDFF requirements for inclusion in the primary analysis population, resulting in approximately 10 participants included in the primary endpoint analysis. Participants who do not meet the MRI-PDFF requirement for primary analysis endpoint will be included in secondary and exploratory analyses.

Demographics and baseline characteristics will be summarized descriptively for all subjects based on the analysis population. Descriptive summaries will include the number of non-missing observations, mean, median, standard deviation, minimum and maximum for continuous results. Categorical results will be summarized with counts and percentages.

## **10. Analysis Populations**

For purposes of analysis, the following populations are defined.

- Enrolled: All participants who complete the onboarding and first time user experience steps within the App for the first treatment cycle assigned. This population will be utilized for all safety summaries;
- Per Protocol: Participants who are enrolled and complete a minimum number of lessons in the App during the intervention period, as pre-specified in the Statistical Analysis Plan (SAP). This population of participants will be the Intent to Treat (ITT) group for analysis;

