|  | 
participants will be screened and consented by the research team, per the procedures listed below. FibroScan will be used to screen individuals likely to meet the PDFF primary endpoint analysis criteria of a liver fat fraction greater than or equal to 10% at baseline. All participants will be included in secondary and exploratory endpoint analysis.
 
Labs and imaging will be collected at screening visit to confirm eligibility requirements and establish a baseline, then again at the end of the intervention to assess therapeutic impact. Participants will also be asked to complete qualitative assessments to evaluate their experience using the study intervention and the impact of treatment on their quality of life.
 
The full Schedule of Assessments is provided in Table 1 within the protocol.
 
The treatment, BT-NCBT-00x, consists of a software as a medical device developed by the study Sponsor, Better Therapeutics. It delivers treatment to participants with cardiometabolic disease, using behavioral therapy that targets individual behaviors related to improving dietary quality and physical activity. BT-NCBT-00x is accessed via the participants' smartphone after downloading from the phone's corresponding app store.
 
Participants will receive behavioral support by the Better Therapeutics patient services team in the form of an orientation and wrap-up call. The intent of the Treatment Orientation Call is to introduce participants to the nature of the treatment and assess readiness to engage in behavioral therapy. In this call, participants will also receive education on evidence-based behavioral strategies for NAFLD treatment that are not yet fully integrated into BT-NCBT-00x, such as the benefit of reducing intake dietary saturated fat and replacing with monounsaturated and polyunsaturated fatty acids. The wrap-up session is intended to allow the Better Therapeutics team to gather feedback about participants' experiences using the intervention. The study population will also be monitored by the Better Therapeutics Population Health Nurse Practitioner and participants will be offered additional behavioral
 |

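### Section 10 declares a set selected on lessons completed to be the Intent to Treat group, which is not ITT and conflicts with the populations stated elsewhere in the protocol

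*Protocol*

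**What the plan says.** Protocol Section 10 (Analysis Populations) lists two sets:

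- **Enrolled**: participants who finish onboarding in the app. Its stated use is the safety summaries.
- **Per Protocol**: "Participants who are enrolled and complete a minimum number of lessons in the App during the intervention period", with the minimum left to the SAP. The entry then ends: "This population of participants will be the Intent to Treat (ITT) group for analysis".

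Sections 11.1 and 11.2, on the efficacy analyses, name no population.

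Other parts of the protocol describe the efficacy populations without any lesson condition:

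- Sections 3.2 and the Synopsis (Secondary Endpoints) define the first secondary endpoint, change in liver fat by MRI-PDFF, over all participants.
- The Synopsis (Study Design) states: "All participants will be included in secondary and exploratory endpoint analysis".
- Section 9 (Sample Size) defines the primary analysis population as those who meet the entry criteria and have baseline PDFF of at least 10%. Section 4.1, item 7, gives the same PDFF condition.

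**The concern.** Intent to treat means that participants are analysed regardless of how far they followed the treatment. The number of lessons completed is known only after treatment starts, and the lessons are a core part of the treatment (Section 5.4). A set that requires a minimum number of them is a per-protocol set, and it cannot also be ITT.

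The label matters because of what it would do to the result. Someone who stops doing lessons but returns for the final MRI would be dropped from the efficacy estimate. Low engagement is foreseen: Section 5.5 plans extra support for users below engagement thresholds. Motivated users plausibly both complete more lessons and improve more, and with no control arm nothing offsets that selection. Efficacy is part of the primary objective and the results are meant to help plan later studies (Section 1). A favourable adherent-user mean reported as ITT would therefore be carried forward under the wrong name.

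**Working it through.** **Step 1. Which set carries efficacy?** Section 10 gives Enrolled a safety role and says Per Protocol is the group for analysis. It defines nothing else, and Sections 11.1 and 11.2 do not choose. The only set left for efficacy is the lesson-defined one. This is an inference from the structure of Section 10, since the word efficacy does not appear there.

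**Step 2. Do the passages agree?**

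| Place | Population | Lesson condition? |
|---|---|---|
| Section 10, Per Protocol/ITT | Enrolled with a minimum of lessons | Yes |
| Section 9, primary analysis population | Eligible, baseline PDFF at least 10% | No |
| Section 3.2, first secondary endpoint | All participants | No |
| Synopsis, Study Design, secondary and exploratory | All participants | No |

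If any participant falls below the lesson minimum, the first row gives a different set from the other three.

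**Step 3. The plan's own figure.** Section 9 reports: "The average mean absolute change in steatosis was -2.4 and mean standard deviation was 1.6". The standardised effect is 2.4/1.6 = 1.5. For a two-sided one-sample t-test at alpha 0.05 (sidedness is not stated), exact noncentral-t power is 90.8% at n = 7 and 95.1% at n = 8. The stated 8 participants for about 90% power is therefore adequate and slightly conservative, and 8/(1 - 0.20) = 10 as stated. The sample size arithmetic is not in dispute. Only the SD of 1.6 and the planned change of 2.4 are carried forward.

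**Step 4. How large could the selection effect be?** The protocol gives neither the lesson minimum nor the share expected to reach it, nor any link between engagement and change, so all three are assumed. Suppose engagement and liver-fat reduction are jointly normal with correlation ρ, and the most engaged fraction k is kept. The mean reduction among those kept then exceeds the mean in everyone by

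bias = ρ × 1.6 × φ(z)/k, where z is the (1 - k) normal quantile and φ the normal density.

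| k kept | φ(z)/k | bias, ρ = 0.3 | bias, ρ = 0.5 | as % of 2.4 |
|---|---|---|---|---|
| 0.95 | 0.1031/0.95 = 0.109 | 0.052 | 0.087 | 2% to 4% |
| 0.80 | 0.2800/0.80 = 0.350 | 0.168 | 0.280 | 7% to 12% |
| 0.60 | 0.3863/0.60 = 0.644 | 0.309 | 0.515 | 13% to 21% |

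**Step 5. Sensitivity to the model.** Suppose instead that completers change by -2.4 and a fraction f of non-completers changes by m. The overstatement is then f × (2.4 - |m|). With f = 0.1 and m = -1.2 it is 0.1 × 1.2 = 0.12 points. With f = 0.4 and m = 0 it is 0.4 × 2.4 = 0.96 points. The direction is the same, but the size depends heavily on what is assumed.

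**The case against.** Several parts of the other side's case stand.

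- **The efficacy assignment is not explicit.** Section 10 says only that the set is for analysis. The inference in Step 1 is strong but remains an inference, and the SAP, which is not available here, may settle it.
- **Some of the apparent conflict is contrast with the PDFF subset.** The all-participants sentence in the Synopsis directly follows the 10% PDFF criterion and was probably written to set the full cohort against that subset. The Section 9 sentence "Participants who do not meet the MRI-PDFF requirement for primary analysis endpoint will be included in secondary and exploratory analyses" says only that people below the cut-off are not lost, which is compatible with a lesson filter and is not relied on here. The first secondary endpoint and the Section 9 definition of the primary population carry the conflict.
- **The bias size is assumed.** A low lesson minimum would make it small, as the 95% row shows.
- **The setting is modest.** This is an uncontrolled feasibility study of about 20 people. There is no randomisation for ITT to protect, and an adherent-user estimate is a legitimate quantity if it is named as one. This limits the consequences but does not make the label correct.

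Three stronger readings are tempting, and the documents do not support them.

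- **That the lesson rule costs power.** Taking 80% of 8 gives 6.4 participants, and at a fixed effect of 1.5 SD power would fall from 95.1% to 86.7% (83.3% at n = 6). That holds the effect fixed while also claiming that selection inflates it. Under the Step 4 model at k = 0.80, power is 92% to 95% at 6.4 and 89% to 93% at 6.
- **That the 20% attrition allowance omits this loss.** Section 9 does not define attrition. Those who abandon the app may largely be those who miss the final MRI, in which case 8 already allows for them.
- **That an ineffective app would show the same spurious reduction.** That needs the correlation to persist with no app effect, for example through motivation alone. The protocol gives no evidence on this.

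**Conclusion.** The concern holds as a defect of definition and labelling. Section 10 calls an adherence-selected set ITT, leaves that set as the only one available for efficacy, and so conflicts with the populations given in Sections 3.2 and 9 and, read literally, in the Synopsis. Leaving the lesson minimum to the SAP is acceptable and is not part of the point.

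The expected direction of bias is in favour of the app, on the assumption that engagement and improvement are positively related and that some low-engagement users return for the MRI. Under the Step 4 assumptions the illustrative range is 0.05 to 0.52 points, or 2% to 21% of the planned 2.4. It is not an estimate for this trial. No claim is made about loss of power or about the attrition allowance.

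**What to change.** In Section 10:

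1. Delete the sentence that makes the Per Protocol set the ITT group.
2. Define the efficacy set as all Enrolled participants regardless of lessons completed: those with baseline PDFF of at least 10% for the primary endpoint, and all Enrolled for the secondary and exploratory endpoints. Use every available end-of-treatment MRI.
3. Keep the lesson-defined set as a supportive analysis, called Per Protocol and nothing else.
4. Name the population in Sections 11.1 and 11.2, and carry the same definitions into the SAP.

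The cost is rewording. Table 1 already schedules the post-intervention MRI without a lesson condition, so no extra participants or visits are needed. The headline estimate may be slightly less favourable.
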